##### Suicide Prevention Pathway (standard care approach)

The SPP comprises seven inter-related clinical steps that are undertaken with consumers presenting with suicidality:
i)Initial screening—persons experiencing suicide ideation and who may also have a history of, or recent, suicide attempt, are placed on the pathway.ii)Comprehensive assessment—assessment of suicide risk through static and dynamic factors. Exploration of suicidal intent based on the comprehensive chronological assessment of suicide events (CASE). The CASE approach examines the presenting suicide event (suicidal feelings, ideation, and intent), recent events (over the last 48 h), recent suicide attempts (2 days to 2 months previously), and past suicide attempts (more than 2 months previously) [27]iii)Formulation of suicide risk—based on a prevention-oriented approach and considers the person’s demographics, culture, history of violence, deliberate self-harm, mental illness, crisis and previous suicide behaviour, current situation (stress, precipitating circumstances), their current risk status (how they compare with a stated population), and risk state (how they compare with themselves at their baseline), their available supports and foreseeable events in their life in order to develop an individualised care plan [28].iv)Safety planning—performed in collaboration with the consumer, prior to leaving the ED, and includes counselling on access to lethal means, provision of brief patient and carer information, and timely referral for face-to-face mental health follow-up [29, 30].v)Structured follow-up—within 24–48 h of discharge, in the community [31].vi)Transition of care plan—“warm handover” is a robust handover to ongoing care services, whether medical/clinical or non-government organisation.

#### Criteria for discontinuing or modifying allocated interventions {11b}

Consumers are made aware (both verbally and written) that they can withdraw consent to participate in the study at any time without any questions asked, or any impact on their ongoing treatment and care. Participants who withdraw from the study are provided with the option of (a) all their collected data being withdrawn from the study or (b) their collected data being used.

#### Strategies to improve adherence to interventions {11c}

Both interventions are delivered in person with each participant. Engagement with the process is noted as part of the clinical intervention and addressed as part of the therapy to facilitate engagement if there are any concerns. Participant clinical progress is discussed in multidisciplinary team (MDT) meetings. Clinical progress and missed sessions are discussed, and strategies for engaging or re-engaging participants are deliberated. This occurs with the recognition of both ASSIP and Brief CBT as standardised, manualised interventions.

The therapy clinician further informs the participant of the therapy processes and expectations. ASSIP and Brief CBT are offered as interventions that are very tightly integrated into the clinical SPP in order to maximise continuity of care and provide the consumer with an integrated care experience, enhancing adherence to interventions. Aspects of the consumer experience and perception of therapy and therapeutic alliance are assessed using the revised Helping Alliance Questionnaire (HAqll).

#### Relevant concomitant care permitted or prohibited during the trial {11d}

Participants can continue to take medications or receive other psychosocial interventions during the study.

#### Provisions for post-trial care {30}

Gold Coast University Hospital and Bond University (the administering institution) will provide insurance cover for the research project (viz., public liability insurance and professional indemnity). Should this study find evidence of the effectiveness of ASSIP or CBT (in addition to TAU) over another treatment arm, consumers will be able to access the effective intervention.

### Outcomes {44}

#### Primary outcome measures

Primary outcomes are the time to representation to hospital with a suicide attempt and proportion representing within 7, 14, 30, and 90 days. Suicidal ideation will also be examined (in a descriptive analysis) to ascertain whether a rise in suicide ideation is commensurate with a fall in suicide attempts (i.e. an increase in help-seeking behaviours). Death by suicide rates will also be examined to make sure that representations with a suicide attempt are not due to participants dying but due to them getting better. Death clearly assessed as not involving self-harm will be represented as not completing the study. Time to suicide attempt is measured by calculating the total number of days from the initial presentation to the re-presenting date for a subsequent suicide attempt. For participants without a subsequent suicide attempt, the total number of days from enrolment to the last assessment (24 months) will be calculated.

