#### Hypotheses

The use of suicide-specific psychological interventions (ASSIP; CBT) combined with a comprehensive clinical SPP will have better outcomes than the clinical SPP alone.Outcomes for the ASSIP + SPP and CBT + SPP will be similar. This hypothesis is exploratory in nature.

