### Sample size {14}

The sample size was calculated on the basis of a time to event analysis of the time to representation for suicidality. From previous studies using CBT as an additional treatment component following attempted suicide [24, 39], we anticipated that the proportion of patients re-presenting for attempted suicide over a 2-year follow-up period will be approximately half that of the TAU group. From recent data from our health service, this represents a decrease from 48 to 24%. To detect this difference (equivalent to a hazard ratio of 0.42) by the log rank test in a proportional hazards time-to-event analysis with 80% power at a two-sided significance level of 5%, we require 132 participants in two groups of 66 each. However, we anticipated a dropout rate of approximately 4.5% per month which would result in 35% of participants completing the full 24-month follow-up (65% total dropout). The effective dropout rate is thus 41%, as those dropping out later contribute proportionately more. When accounting for this dropout rate, to maintain the same power, a total of 137 participants in each of the three cohorts are required for a total of 411 in total.

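### Five outcomes share primary status without ranking, but only time to re-presentation is powered and given an analysis; it should be named the single primary outcome

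*Protocol article*

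**What the plan says.** Under Primary outcome measures, the protocol article states: "Primary outcomes are the time to representation to hospital with a suicide attempt and proportion representing within 7, 14, 30, and 90 days". No order of importance is given. The abstract and the Discussion also speak of primary outcomes in the plural.

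Objectives {7} sets two comparisons on these outcomes: ASSIP + SPP against SPP, and CBT + SPP against SPP. The comparison of the two therapies is set apart under Hypotheses: "This hypothesis is exploratory in nature".

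Sample size {14} rests on one outcome: "The sample size was calculated on the basis of a time to event analysis of the time to representation for suicidality". It assumes a halving of the two-year proportion ("this represents a decrease from 48 to 24" per cent), "equivalent to a hazard ratio of 0.42", tested "by the log rank test in a proportional hazards time-to-event analysis with 80% power at a two-sided significance level of 5" per cent. This is the only significance level in the article, and no division of it is mentioned.

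The statistical methods section {20a} names the log-rank test, Cox shared frailty models and parametric mixed models for time to re-presentation. It names nothing for the four proportions.

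Time to attempt is counted from the initial presentation (Primary outcome measures). Participants are approached 48 to 72 hours after the event {26a}. Allocation follows consent {16b}, and the therapy appointment is booked after that {16c}.

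**The concern.** Which outcome is primary is something a protocol fixes, and this one fixes five at equal rank. The sample size and the named analysis single out time to re-presentation, but the outcome section does not, so the sections disagree about what decides the trial. Read as written, a difference at any one of the windows, for either therapy, could be reported as a positive primary result even if time to re-presentation showed nothing. Conversely, the four proportions carry primary status in a trial not sized for them, so a null result on them would say little.

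The earliest windows have a further weakness: they cover days when a participant may not yet have been randomised or have started therapy, which dilutes any effect.

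**Working it through.** **Inputs from the article.** Two-year event proportions 48% (SPP) and 24%; hazard ratio 0.42; two-sided 5%; 80% power; 66 per group before dropout; effective dropout 41%; 137 per arm; two comparisons with SPP.

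**1. The plan's own figure.** The hazard ratio is ln(0.76)/ln(0.52) = 0.420, as stated. Freedman's formula gives (1.960 + 0.842)² × (1.42/0.58)² = 7.849 × 5.994 = 47.0 events, so 47 or 48 with rounding. Dividing by the mean event proportion 0.36 gives 131 to 133, which agrees with "we require 132 participants in two groups of 66 each". So 132 is the size for one log-rank comparison at an undivided 5%.

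The next step does not follow at that alpha: 66/(1 − 0.41) = 112, not 137. At 2.5% Freedman gives 57 events, 57/0.72 = 79.2, so 80 per arm, and 80/0.59 = 136. The final number therefore fits a 2.5% level that the text does not state.

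**2. Expected events and power in the windows.** The article gives no early event rates, so a shape must be assumed. Cumulative hazard to day t is −ln(0.52) × (t/730.5)^k in SPP and −ln(0.76) × (t/730.5)^k with therapy. k = 1 is a constant hazard; k = 0.75 and k = 0.5 are assumed degrees of front-loading. Power is for two proportions at 137 per arm, two-sided 5%, normal approximation.

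| Window | k = 1: events SPP vs therapy | power | k = 0.75: power | k = 0.5: events | power |
|---|---|---|---|---|---|
| 7 days | 0.9 vs 0.4 | 7% | 12% | 8.5 vs 3.6 | 30% |
| 14 days | 1.7 vs 0.7 | 9% | 18% | 11.9 vs 5.1 | 39% |
| 30 days | 3.6 vs 1.5 | 15% | 28% | 17.0 vs 7.4 | 53% |
| 90 days | 10.6 vs 4.6 | 36% | 54% | 28.1 vs 12.6 | 75% |

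Under k = 1 the first two power figures are generous: the normal approximation is poor at such counts, and simulation with chi-square tests gives about 1% and 5%. A Fisher test at 137 versus 137 needs at least 6 versus 0 events for p < 0.05. No window reaches 80% in any scenario.

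**3. False-positive rate if every primary outcome were tested at 5%.** Ten independent tests would give 1 − 0.95^10 = 40%, but these are not independent: the windows are nested, they overlap with the log-rank test, and the two comparisons share the SPP arm. Simulated null trials (137 per arm, 48% in every arm, 6,000 per scenario, the three values of k) give:

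- the two log-rank tests alone: about 9%;
- all ten tests, uncorrected chi-square for the windows: about 25% to 30%;
- all ten tests, Fisher for the windows: about 15% to 20%;
- the five outcomes within one comparison: about 14% to 16% with chi-square and 8% to 10% with Fisher. Single scenarios varied by a point or two between runs.

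**4. Power with one primary outcome.** Expected events per comparison are 2 × 137 × 0.59 × 0.36 = 58.2. At 5% per comparison, power is 88% (Freedman) to 91% (Schoenfeld); at 2.5% it is 81% to 86%.

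**5. Timing.** If the windows start at initial presentation, two to three days have passed before a participant is approached. Time to consider, consent, allocation and booking follow. Much of the first week, and part of the second, then lies before therapy can act.

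**The case against.** The strongest reply is that time to re-presentation already leads by implication: the sample size and the analysis section are built on it alone. The rules for the proportions may sit in an analysis plan that is not shown. The first part is fair, and it is why the main analysis survives. But the ranking of primary outcomes belongs in the protocol, and the outcome section contradicts the implied one.

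Several stronger readings are tempting and do not hold.

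- *A chance primary success is likely.* It is not: 15% to 30% is three to six times the nominal 5%, but well below one half. With exact tests and a constant hazard, the 7- and 14-day windows add almost nothing, because so few events cannot reach significance.
- *The windows contain almost no events.* This fits 7, 14 and 30 days under a constant hazard. It does not fit 90 days (about 15 events over two arms), and it fits no window if risk is strongly front-loaded.
- *All four windows mostly precede completed therapy.* The text gives no session spacing and the schedule figure is not shown. The timing point is supported at 7 days and partly at 14. It also assumes that the windows use the clock defined for time to attempt, which the article does not say.
- *Ten tests at 5% are planned.* No test or alpha is stated for the proportions; that they would be tested is inferred from their primary status.
- *Alpha was certainly not divided.* The 137 per arm fits 2.5% per comparison, so a split may have been used without being stated.

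It is also arguable that two different therapies, each with its own comparison, need no mutual adjustment. The problem then shrinks to about 8% to 16% within one comparison, but does not vanish.

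**Conclusion.** The point stands in limited form. Five outcomes have equal primary status across two comparisons, while one is powered and analysed. The false-positive figures are conditional on all outcomes being tested at 5%. The window power figures rest on the article's 48% and 24% together with an assumed hazard shape, but the conclusion that no window is adequately powered holds for every shape tried. The defect leaves open which result decides the trial; it does not invalidate the log-rank comparison, which the planned 411 participants support. It should be corrected, and with 12 participants recruited at the time of the article the change could still be made early.

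**What to change.** - Name time to first re-presentation with a suicide attempt over 24 months as the single primary outcome. The word first matters, because the analysis section also allows for multiple re-presentations; models for those become supporting analyses.
- Make the 7-, 14-, 30- and 90-day proportions secondary, estimated from the Kaplan-Meier curves with confidence intervals, and state the day from which they are counted.
- State the alpha for the two comparisons with SPP. If an overall 5% is wanted, 2.5% each (or Holm) keeps about 81% to 86% power at 137 per arm with 41% effective loss. If 5% per comparison is intended, say so and give the reason. Either way, bring the step from 66 to 137 into line with the stated level.

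The cost is wording and a registry update, with no extra participants. The proportions lose primary status but are still reported.

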### Data collection and management

#### Plans for assessment and collection of outcomes {18a}

Each person who presents to Gold Coast Health is assigned a unique identifying, or UR, number. The Emergency Information System at Gold Coast Health (viz., FirstNet database) records all ED presentations. The ED presentations will be interrogated for the UR number of all study participants, and any presentation within 24 months of an initial presentation will be reviewed for evidence of suicidality. Multivariate Cox proportional hazard regression models will be used to analyse time to re-presentation for a suicide attempt. Time to suicide attempt is measured by calculating the total number of days from the initial presentation (not including days of admission for some consumers with medical and/or psychiatric admission) to the re-presenting date for a subsequent suicide attempt.

For secondary outcomes, data are collected by the RA at five time points: (1) baseline, (2) end of CBT or ASSIP interventions, (3) 6 months, (4) 12 months, and (5) 24 months from baseline. At baseline, demographic data and psychometric data are collected in person or via the telephone with the RA, as outlined below. At end of treatment and 6, 12, and 24 months, psychometric data are collected. Therapeutic alliance is assessed at the completion of the interventions. Cost comparisons will be based on service information regularly collated by GCMHSS and ED (e.g. contact hours, bed stays, ED visits). Study completion will be analysed post hoc, as a secondary outcome.
i)Demographic data: includes age, gender, method of suicide attempt, employment status, education history, place of residence, living situation, marriage status, family contact, known diagnoses and co-occurring conditions (e.g. drug and alcohol use), and history of service provision, including use of psychological interventions

It is anticipated that a number of people within the study population will be from specific cultural groups, who may also be high-risk populations, such as Aboriginal and Torres Strait Islander people, people from cultural and linguistically diverse (CALD) communities, people who identify as LGBTQI, older persons (aged over 60 years), and young people (aged 16–18 years). Questions are included to enable the identification of these specific target population subgroups.

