## Statistical methods

### Statistical methods for primary and secondary outcomes {20a}

To determine the effectiveness of additional CBT + SPP or ASSIP+SPP compared with SPP alone, univariate (log rank test) and multivariate Cox proportional hazard shared frailty regression models and multilevel mixed effects parametric models will be used to analyse time to re-presentation for suicide attempts [35]. Time to suicide attempt is measured by calculating the total number of days from the initial presentation (with days of psychiatric admission for some consumers taken into account), to the re-presenting date for a subsequent suicide attempt and may include multiple representations [35]. For participants without a subsequent suicide attempt, the total number of days from enrolment to the last assessment (24 months) will be calculated. All collected demographic and clinical variables will be considered in the model-building process. Variables with *P* ≤ 0.1 on univariate analysis will be included in all combinations and retained in the model if *P* < 0.05. Plausible interactions of retained variables will be tested. Collinearity of potential model variables will be assessed using the variance inflation factor. Where appropriate, the proportional hazards assumption will be tested using Schoenfeld residuals. Kaplan-Meier plots will allow visual comparisons between the groups. Analyses will be undertaken on an intention to treat basis. Stata 15 (Stata Corp. College Station, TX, USA) will be used for statistical analyses.

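### The primary event is a hospital re-presentation, so a suicide death without one is not an event, and the article states no rule for how it enters the primary analysis

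*Protocol article*

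**What the plan says.** All references are to the protocol article.

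- **Event.** The section on outcomes, {44}, defines it in its opening sentence: "Primary outcomes are the time to representation to hospital with a suicide attempt and proportion representing within 7, 14, 30, and 90 days".
- **Event date.** Statistical methods {20a} counts days from the initial presentation "to the re-presenting date for a subsequent suicide attempt and may include multiple representations".
- **Event source.** Plans for assessment and collection of outcomes {18a} searches the health service's ED database for each participant: "any presentation within 24 months of an initial presentation will be reviewed for evidence of suicidality". No other source for the primary outcome is described.
- **Suicide death.** Primary outcome measures: "Death by suicide rates will also be examined to make sure that representations with a suicide attempt are not due to participants dying". The abstract says the same in other words.
- **Other deaths.** Primary outcome measures: "Death clearly assessed as not involving self-harm will be represented as not completing the study". This is the only explicit rule for any death.
- **Time for everyone else.** Statistical methods {20a}: "For participants without a subsequent suicide attempt, the total number of days from enrolment to the last assessment (24 months) will be calculated". The abstract and Primary outcome measures carry the same rule, and none of the three places makes an exception for a participant who has died.

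**The concern.** Suicide is the most severe form of the outcome that the trial tries to prevent, and it also stops a participant from re-presenting. If it is not an event, a fatal first repeat lowers the event count of its arm, while a non-fatal one raises it. An arm with more fatal first repeats could then look better on the log-rank test, on the Cox model and on the early proportions.

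The authors saw this risk, which is why they plan to look at suicide rates. But a look alongside does not change the primary estimate. The article gives no combined endpoint, competing-event method or decision rule that would tell a reader what to conclude if the two pointed in different directions.

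**Working it through.** **1. What happens to a suicide death without a re-presentation.** The event needs a re-presenting date and is found among ED presentations. A participant who dies outside hospital has neither, so no event can be recorded. Two consequences follow.

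- *Time to event.* The only time rule left is the one to the 24-month assessment. Taken literally, a death at month m adds 24 − m event-free months after death: 23, 18 or 12 months for a death at month 1, 6 or 12. Three such deaths add 69, 54 or 36 person-months and no event.
- *Proportions at 7, 14, 30 and 90 days.* Under intention to treat ({16a}, {20c}) the person stays in the denominator and is absent from the numerator, and so counts as not re-presenting. Censoring is not defined for a simple proportion.

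**2. The plan's own figure.** Sample size {14} expects 48% re-presenting over two years under control and half that with therapy ("this represents a decrease from 48 to 24" percent), "equivalent to a hazard ratio of 0.42) by the log rank test".

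- HR = ln(1 − 0.24) / ln(1 − 0.48) = 0.420, as stated.
- Freedman's formula (80% power, two-sided 5%) gives 47 events, or 48 with the HR rounded to 0.42. Dividing by the mean event rate of 0.36 gives 130.6 to 133.3 participants, or 65.3 to 66.7 per group. The stated 66 per group reproduces.

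These figures count re-presentations only.

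**3. Size under the one ratio in the article.** Background {6a} cites a community survey with 23 attempts per suicide. Using it here is an assumption, since it does not describe hospital re-presenters. With 137 per arm and full follow-up:

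- expected suicides: control 137 × 0.48 / 23 = 2.9; each therapy arm 137 × 0.24 / 23 = 1.4; about 5.7 in all. Planned dropout would lower the number observed.
- if none of them had a re-presentation, the combined rates are 0.48 × 24/23 = 50.1% and 0.24 × 24/23 = 25.0%.
- HR = ln(0.7496) / ln(0.4991) = 0.415, against 0.420.

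**4. A labelled worst case.** Put three unrecorded suicides in one therapy arm and none in control. Events there go from 137 × 0.24 ≈ 33 to 36, or 26.3%. HR = ln(0.737) / ln(0.52) = 0.466.

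**5. A range of assumed suicide risks.** With s as the 24-month risk of suicide without a re-presentation, the combined rate is 1 − (1 − p)(1 − s).

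| Assumed s | HR with suicide as an event |
|---|---|
| none | 0.420 |
| 1%, 2%, 3%, 5% in both arms | 0.428, 0.437, 0.446, 0.462 |
| 2%, 3%, 5% in the therapy arm only | 0.451, 0.466, 0.498 |

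If suicide deaths are not events and are carried to 24 months, every row would still show 0.42.

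**The case against.** **The 24-month credit is an inference.** A reader might conclude that the plan scores a suicide as 24 months free of attempt. No sentence says so. The time rule covers people without a further suicide attempt, and a suicide can be read as a fatal attempt. Singling out deaths that do not involve self-harm hints that self-harm deaths were meant to be handled differently, and a participant who has died has no 24-month assessment. This stands: the literal reading is not an explicit rule. But the different handling is never stated, and the death would still lack the re-presenting date that the event requires.

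**Detail may sit elsewhere.** Censoring dates and competing-risk analyses are commonly left to the full protocol or the analysis plan. That is fair for those details. The definition of the primary event is not such a detail: the article fixes one, and suicide death is outside it. Censoring at death would remove the false follow-up time, but it would treat the most severe form of the outcome as uninformative.

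**The bias is anticipated.** Suicide deaths are to be examined under the primary outcome measures, so an imbalance should be visible. That stands, but visibility does not correct the estimate.

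**The numerical effect may be negligible.** A reader might take the move from 0.42 to 0.47 as the expected bias. The documents do not support that. It places three deaths in one therapy arm, where the 23:1 ratio gives 1.4, and none in control, where it gives 2.9. Even this shift is small against sampling error: with 33 and 66 events, SE(log HR) = √(1/33 + 1/66) = 0.21, a 95% interval of about 0.28 to 0.64. A suicide that followed a re-presentation, or occurred after arrival at hospital, may already be counted.

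**A pure re-presentation endpoint is defensible.** It matches the service-use question and the sample-size basis, with suicide reported separately. It would then need a stated treatment of suicide as a competing event.

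**Conclusion.** The point holds as one of validity. As defined, a suicide death without a re-presentation cannot be an event in the log-rank or Cox analysis or in the early proportions, and the article does not say when such a person's follow-up ends. The direction of the possible error is clear: fatal first repeats are missing from the count of failures, so an arm with more of them could look better.

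The size is unknown, because the documents give no suicide rate for this population. Under the community ratio applied to both arms, the HR is about 0.415, in effect unchanged. The worst case is about 0.47. Both calculations assume full follow-up and that none of the suicides had a recorded re-presentation. Few and balanced deaths would matter little; a difference between arms would matter more. The point does not rest on a demonstrated numerical shift, nor on any statement in the plan that suicide counts as success.

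**What to change.** - Define the primary event as the first of re-presentation to hospital with a suicide attempt or death by suicide, dated at occurrence.
- Apply the same definition to the 7-, 14-, 30- and 90-day proportions.
- End the follow-up of participants who die from other causes at the date of death.
- Report the attempt-only version, with suicide as a competing event, as a sensitivity analysis, and keep the count of suicides by arm.
- Name a source for the date and cause of death.

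**Cost.** The endpoint becomes a composite and the registry entry needs an update. The death source is more than a change of wording, because only the ED database is described. The change would come after recruitment began, but Trial status reports only 12 people recruited when the article was written. If the authors already meant suicide to count as a further attempt, a sentence saying so, with the dating rule and the data source, settles most of the point.
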